#### Ankle-brachial index

2.5.12

The volunteer will remain at rest, lying supine on a stretcher for 5 min in a quiet environment with a temperature around 25 °C. After that, blood pressure will be measured in the arms and legs, positioning the cuffs of automatic blood pressure devices (BP3AC1, Microlife, Shenzhen, China) approximately 2 cm above the cubital fossa and 2 cm above the malleoli, respectively. After placing the cuffs, blood pressure will be measured simultaneously, first on the right side and then on the left side [17].

The Ankle-Brachial Index (ABI) calculation will be performed using the following formula: ABI = Highest Ankle Systolic Blood Pressure/Highest Arm Systolic Blood Pressure. After determining the ABI, patients will be classified as normal ABI: 0.91 to 1.30) and abnormal ABI: ≤0.90 or >1.30 [17].

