**ASSESSMENTS**						
Clinical (DXA, skinfolds, ABI)		X			X	X
Biochemical (BNP/NT-proBNP, microRNA)		X			X	X
Functional (CPET, 6MWT, sit-to-stand)		X			X	X
Imaging (transthoracic echocardiogram)		X			X	X
Strength (1RM test and retest)		X	X	X (adjustment)	X	X
Strength (isokinetic & handgrip)		X			X	X
Quality of life (Minnesota MLHFQ)		X			X	X
Clinical events & hospitalizations				X	X	X

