#### Exclusion criteria

2.4.2

Any absolute or relative contraindication to exercise testing or training according to international guidelines; History of a major cardiovascular event (e.g., acute myocardial infarction, unstable angina) or cardiovascular procedures (e.g., percutaneous coronary intervention, coronary artery bypass grafting) within the 2 months preceding enrollment; Implantation of a fixed-rate pacemaker where the upper heart rate limit is programmed below the target heart rate calculated for physical training; Specific contraindications to blood flow restriction therapy, including a documented history of deep vein thrombosis (DVT), peripheral vascular disease, active thrombophlebitis, or severe peripheral neuropathy; Inability to perform resistance training due to severe orthopedic or cognitive limitations.

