#### Vascular occlusion pressure calibration

2.5.8

For the BFRRT group, the total arterial occlusion pressure (AOP) will be determined in the fourth week and reassessed alongside the submaximal 1RM tests to account for anatomical and localized adaptations. Measurements will be performed by a trained investigator using a portable vascular Doppler probe (DV 610 B, Medmega, Brazil) to detect the cessation of the auscultatory pulse.

Vascular occlusion will be applied using a clinical blood flow restriction system equipped with a removable aneroid manometer and high-resistance velcro cuffs (Avanutri, Rio de Janeiro, Brazil). To standardize application, the baseline AOP measurement will be performed while the patient is positioned in a relaxed, standing orthopedic posture (anatomical position). The restriction pressure during the sessions will be dynamically calibrated and monitored in real time via the integrated aneroid gauge, set at a standardized, individualized target of 50% of the total AOP for both the upper and lower limbs. The cuffs will remain continuously inflated throughout the specific exercise execution and its corresponding 45-s inter-set rest intervals; however, the cuffs will be completely deflated immediately upon completion of the final set of each exercise and will remain deflated during transitions between different exercise stations to ensure patient safety and comfort.

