#### Procedures

2.5.9

During the first two weeks, participants will undergo comprehensive baseline clinical evaluations. Body composition will be assessed via dual-energy X-ray absorptiometry (DXA) as the primary laboratory standard; additionally, skinfold thickness measurements will be collected as a methodological safeguard and field-based backup to ensure data continuity throughout the long-term trial. Vascular health, cardiorespiratory fitness, and functional performance will be evaluated using the ankle-brachial index, cardiopulmonary exercise testing (ergospirometry), the 6-min walk test, and the 30-s sit-to-stand test.

Muscle strength will be assessed through knee-joint isokinetic dynamometry and handgrip strength. Furthermore, biochemical analyses will be performed to measure blood-borne biomarkers: hemostasis markers (D-dimer, fibrinogen, and activated partial thromboplastin time—aPTT) will be monitored as a clinical safety protocol, alongside systemic inflammatory markers (C-reactive protein) and tissue-specific microRNAs (vascular, skeletal muscle, and cardiac-specific).

Cardiac structure and function will be analyzed via resting transthoracic echocardiography, while health-related quality of life will be measured using the Minnesota Living with Heart Failure Questionnaire.

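### The ankle-brachial index is built from the higher ankle pressure, so a patient with one low leg and one normal leg is classed normal and a one-leg fall is largely hidden

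*Protocol article*

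**What the plan says.** Section 2.5.12 (Ankle-brachial index) uses automatic cuffs on the arms and just above the malleoli, and states that "blood pressure will be measured simultaneously, first on the right side and then on the left side". It then gives a single formula, "ABI = Highest Ankle Systolic Blood Pressure/Highest Arm Systolic Blood Pressure", followed by the rule that "patients will be classified as normal ABI: 0.91 to 1.30", with values of 0.90 or less, or above 1.30, called abnormal. It gives no index per leg and no rule for legs that disagree.

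Section 2.5.9 (Procedures) gives the purpose: "Vascular health, cardiorespiratory fitness, and functional performance will be evaluated using the ankle-brachial index", among other tests. Table 1 schedules the index at baseline (T0), month 4 (T1) and month 12 (T2).

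Two other sections bear on why it matters. Section 2.4.2 excludes patients with "Specific contraindications to blood flow restriction therapy, including a documented history of deep vein thrombosis (DVT), peripheral vascular disease" and other conditions. Section 2.5.8 sets the cuff pressure in the blood flow restriction arm (BFRRT) at "50% of the total AOP for both the upper and lower limbs".

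**The concern.** An ankle-brachial index is used to find a leg with reduced pressure. Taking the higher ankle pressure across the two legs does the reverse, because it reports the healthier leg and drops the other. One-sided low pressure then disappears from the record although both pressures were measured.

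Two things are at stake. At T0, some patients with one low leg would be labelled normal before half of the trial's participants have their legs cuffed. At T1 and T2, a fall in one leg would show as no change or as a smaller change than occurred. Peripheral vascular disease is a listed contraindication to blood flow restriction, so this is information the investigators would want, and the formula discards it.

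**Working it through.** The plan gives no worked value of the index, so there is no figure to reproduce. The check applies the stated formula and cut-offs to example pressures (chosen for illustration) and compares the result with the index of each leg.

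**Formulas**
- As written: index = max(right ankle, left ankle) / max(right arm, left arm).
- Per leg: index = that leg's ankle pressure / max(right arm, left arm).
- Class (section 2.5.12): normal 0.91–1.30; abnormal 0.90 or less, or above 1.30.

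**Classification**

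| Ankles (mmHg) | Higher arm | As written | Legs |
|---|---|---|---|
| 135 and 95 | 130 | 135/130 = 1.04, normal | 1.04 and 0.73 |
| 140 and 110 | 135 | 140/135 = 1.04, normal | 1.04 and 0.81 |
| 185 and 95 | 130 | 185/130 = 1.42, abnormal | 1.42 and 0.73 |

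The third row marks the limit of the fault: a leg above 1.30 is still flagged. What is lost is a low leg paired with a leg at 0.91–1.30. A grid in steps of 0.01, with one leg at 0.40–0.90 (51 values) and the other at 0.91–1.30 (40 values), gives 51 × 40 = 2040 pairs. All 2040 are classed normal, as taking a maximum requires.

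**Change from T0 to T1.** Start from ankles 135 and 130 with arm 130, so the legs are at 1.04 and 1.00 and the stated index is 1.04.
- The second leg falls to 100: the stated index is 135/130 = 1.04, a change of 0.00. That leg goes from 1.00 to 100/130 = 0.77, a change of −0.23.
- The first leg falls to 100: the stated index is 130/130 = 1.00, a change of −0.04. That leg goes from 1.04 to 0.77, a change of −0.27.

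A fall in the lower leg is fully hidden. A fall in the higher leg shows only down to the level of the other leg.

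**How many patients.** The documents give no prevalence of one-sided low values. If 2–10% of the 52 participants were affected (an assumption), that would be 1.0 to 5.2 patients in the trial, or 0.5 to 2.6 among the 26 allocated to BFRRT.

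**Chance flags under a per-leg rule.** Assume both legs are truly at 1.05, with independent, normally distributed error in each leg. Let p be the probability that one leg reads 0.90 or less, or above 1.30.
- Either-leg rule: 1 − (1 − p)².
- Stated rule: P(both legs 0.90 or less) + P(either leg above 1.30).

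| Error SD | p | Either leg | × 52 | Stated rule | × 52 |
|---|---|---|---|---|---|
| 0.05 | 0.0014 | 0.27% | 0.1 | 0.0% | 0.0 |
| 0.08 | 0.0313 | 6.2% | 3.2 | 0.3% | 0.1 |
| 0.10 | 0.0730 | 14.1% | 7.3 | 1.7% | 0.9 |

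**The case against.** The strongest reply is that the formula may be meant for each leg in turn, with the highest of several readings in that leg. The article does not state the number of readings, it is a condensed text, and the source it cites for the method is not at hand. This reading cannot be ruled out, but the text does not support it. One automatic cuff per ankle is described, with no separate ankle arteries and no repeats; the matching term for the arms most naturally means the higher of the two arms; and the class is assigned to patients. If a per-leg value was intended, the wording still needs to change so that staff compute it.

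The second reply is that nothing formal rests on the index. It is neither a primary nor a secondary outcome, the analysis section does not name it, and no rule ties it to eligibility or cuff use. Other safeguards exist: peripheral vascular disease is an exclusion, and occlusion pressure is set individually by Doppler in the BFRRT arm. All of that stands, and it limits the weight of the point. It also means there is no contradiction with section 2.4.2. It does not make the stated rule right for a measure taken three times to evaluate vascular health.

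Third, the remedy adds false alarms. At an error SD of 0.08 or 0.10, the 3 to 7 chance flags could match or outnumber the illustrative 1 to 5 true cases. That is fair, and it is a reason to send a flag to clinical review and not to automatic exclusion.

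Finally, the loss can be undone later if both ankle pressures are kept. That holds for analysis, but a warning recovered after the intervention comes too late to inform cuff use.

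**Conclusion.** The concern holds. As written, the index takes the better leg, so every patient with one leg at or below 0.90 and the other at 0.91–1.30 is classed normal. A fall confined to one leg is hidden entirely or reduced; in the worked cases a true change of −0.23 or −0.27 is reported as 0.00 or −0.04. High values in one leg are not affected.

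This rests on reading the formula as one value per patient, which is the natural reading but not a certain one. The number of patients affected cannot be taken from the documents. The consequence is a misclassified vascular measure and a missed baseline warning. The primary and listed secondary outcomes are untouched. The formula should be corrected, but the point does not threaten the trial's main conclusion.

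**What to change.** Reword section 2.5.12 as follows:
- Compute the index separately for the right and left leg, as that leg's ankle systolic pressure over the higher of the two arm systolic pressures, and record both values.
- Class the patient as abnormal if either leg is 0.90 or less, or above 1.30.
- Report change at T1 and T2 for each leg.

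What an abnormal T0 value means for cuff use is for the clinical investigators to decide.

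The cost is a change of wording; the pressures are already taken. The price is some extra reviews prompted by measurement error: about 0.1, 3 or 7 of 52 at the assumed error SDs of 0.05, 0.08 or 0.10, against about 0, 0.1 or 0.9 under the present formula.

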#### Ergospirometry test

2.5.13

The maximal cardiopulmonary exercise test (CPET) will be performed on a motorized treadmill (Millennium ATL, Imbramed, Porto Alegre, Brazil) utilizing an individualized ramp protocol [18], designed to elicit volitional exhaustion within 8–12 min. The primary objective is to evaluate electrocardiographic and hemodynamic responses, alongside peak oxygen consumption (VO2 peak), during progressive physical exertion. Continuously recorded 3-lead electrocardiographic signals (CM5, D2M, and V2M) will be captured via a portable digital electrocardiograph (MEBT-100, Micromed, Brazil) using solid-gel silver/silver-chloride adhesive electrodes (Kendall, Cardinal Health 200, USA) affixed to the patient's chest following thorough skin preparation with gauze and 70% isopropyl alcohol.

Systolic and diastolic blood pressures will be monitored minute-by-minute using a calibrated manual aneroid sphygmomanometer (Welch Allyn, Chicago, IL, USA). To quantify metabolic gas exchange, a breath-by-breath automated respiratory gas analyzer (Cortex Metalyzer, Leipzig, Germany) will be deployed, with metabolic data continuously aggregated and recorded every 10 s.

Participants will receive strict pre-test instructions to arrive at the laboratory well-hydrated, appropriately nourished, and wearing athletic clothing. Consumption of caffeine-containing foods or beverages and tobacco smoking will be strictly prohibited for at least 2 h preceding the evaluation, and strenuous physical exertion will be restricted for 24 h prior to testing. Additionally, male participants will undergo chest hair trichotomy at the electrode placement sites to maximize signal quality.

For standardization, all evaluations will be scheduled during morning hours and will be continuously supervised by a clinical cardiologist. To ensure patient safety, the test will be immediately terminated upon volitional exhaustion, or prior if absolute clinical indications for termination manifest, including progressive drops in systolic blood pressure, severe chest pain indicative of angina, complex ventricular arrhythmias, or horizontal/downsloping ST-segment depression greater than 2.0 mm [19].

#### 6-Minute walk test

2.5.14

The test will be performed to assess submaximal aerobic endurance and functional walking capacity. The testing course will be set up in a long, flat corridor where two cones will be placed 30 m apart, with distinct visual markings positioned every 5 m between them. Participants will be instructed to walk continuously around the course for 6 min, attempting to cover the maximum possible distance without running or jogging. A trained investigator will be responsible for tracking and recording the total distance covered, providing standardized phrases of encouragement and announcing the remaining time every minute. If severe dyspnea or fatigue manifests, participants will be permitted to stop, rest on a chair, and resume walking as soon as they feel capable [20].

#### Sit-to-stand test

2.5.15

The test will be performed to assess the functionality, power, and muscle endurance of the lower limbs, in addition to being an indicator of mobility and functional balance. At the command of “attention, go!”, volunteers will sit down and stand up from a chair (without the aid of the upper limbs) as many times as they can in 30 s [20].

The test will start with the volunteer seated, with their back supported, feet shoulder-width apart (fully supported on the floor), and upper limbs crossed. When standing, they will fully extend the trunk, and when returning to the starting position, they will fully rest their buttocks on the seat. A researcher will observe the test and count only correct executions. Verbal guidance will be provided to correct incorrect executions. A chair without arms, with a seat height of approximately 43 cm will be used, and for safety reasons, it will remain supported against a wall [20].

#### Isokinetic test

2.5.16

To measure the isokinetic muscle strength and power of the quadriceps and hamstrings, the Biodex System 3 isokinetic dynamometer (Biodex Medical Systems, New York, USA) will be used. Before each test, participants will warm up on a cycle ergometer (Ergomedic 828 E, Monark, Vansbro, Sweden) for 5 min with a workload of 50 W [21]. The dynamometer configurations and axis alignment will be adjusted as suggested by Stumbo et al. (2001) [22].

During the test, participants will be secured with the equipment stabilization belts to minimize cooperation from other non-specific muscle groups [22]. At the command of “attention, go!”, participants will perform five maximal repetitions of knee extension and flexion using the maximum possible force, maintaining a standardized range of motion of 70°. The test will be performed on both legs in a concentric/concentric mode, utilizing two angular velocities (60° per second and 180° per second) with a 1-min recovery interval between them.

All participants will be vigorously encouraged verbally during the execution. The primary outcome variables extracted from the software will comprise peak torque, total work, and power.

#### Handgrip strength

2.5.17

The test will be measured with a JAMAR hydraulic handgrip dynamometer (Sammons Preston Inc., Illinois, USA). During the test, participants will be seated in an armless chair with an erect trunk posture, the elbow flexed at 90°, and the forearm maintained in a neutral semi-pronation position. The grip on the dynamometer will be individually adjusted according to the size of the hands, ensuring the inner bar closest to the body of the dynamometer remains positioned precisely on the second phalanges of the index, middle, and ring fingers [23].

Two measurements will be taken on each hand alternately, respecting a 1-min resting interval between attempts. The test will start with the command “attention, go!”, and participants will squeeze the dynamometer gradually until reaching absolute maximum force, avoiding any compensatory radial or ulnar wrist deviation. The highest peak force value reached in each hand will be considered as the definitive reference metric.

#### Biochemical tests blood

2.5.18

Blood samples will be collected via venipuncture after a strict 12-h overnight fast. All laboratory analyses will be executed at the central facility of the Catholic University of Brasília. Approximately 28 aliquots per participant will be prepared for immediate storage in liquid nitrogen at the facility, and 14 aliquots will be stored in ultra-low temperature freezers at minus 80 °C at the research center for future exploratory biomarker analyses.

The comprehensive laboratory panel will include whole blood cell count determined via an automated counter method. Metabolic and lipid profiles will comprise fasting plasma glucose, total cholesterol, high-density lipoprotein cholesterol, and triglycerides, all analyzed using the ADVIA Chemistry system (Siemens, Deerfield, Illinois). Low-density lipoprotein cholesterol will be calculated utilizing the Friedewald equation, or measured directly if triglyceride levels exceed 400 mg per deciliter.

To evaluate systemic inflammatory responses, organ function, and clinical safety markers, the panel will analyze high-sensitivity C-reactive protein and fibrinogen (Dade Behring; Siemens); creatinine, uric acid, calcium, gamma-glutamyl transferase, aspartate aminotransferase, and alanine aminotransferase (ADVIA Chemistry); glycated hemoglobin (Bio-Rad Laboratories, Hercules, California); and creatine phosphokinase to monitor skeletal muscle integrity.

Endocrine regulation and cardiac strain will be determined via thyroid-stimulating hormone, thyroxin, insulin, and C-peptide (Siemens). Crucially, N-terminal pro-brain natriuretic peptide (Dade Behring; Siemens) will be quantified as a primary biomarker of myocardial wall stress, and microalbuminuria (Dade Behring) will be assessed to track baseline microvascular renal function. These biochemical markers will be utilized to ensure patient safety compliance regarding renal and hepatic thresholds prior to exercise, and to serve as clinical baseline covariates.

#### Transthoracic echocardiogram

2.5.19

Echocardiographic images will be acquired according to the clinical recommendations of the American Society of Echocardiography using a commercially available Philips Affiniti 70 ultrasound system (Philips Ultrasound, Andover, Massachusetts, USA) equipped with a X5-1 transducer operating between 1 and 5 MHz.

The assessment of diastolic dysfunction and reduced left ventricular ejection fraction (defined as less than or equal to 54 percent for women and less than or equal to 52 percent for men) will be characterized according to current consensus guidelines [24,25]. Left ventricular end-diastolic diameter, interventricular septum thickness, and left ventricular posterior wall thickness will be measured at end-diastole. Left ventricular mass will be calculated according to the Devereux formula [24].

The left ventricular mass index will be calculated by dividing the total left ventricular mass by the body surface area, with the latter determined using the Mosteller formula [26]. Ventricular hypertrophy will be defined as a left ventricular mass index greater than or equal to 102 g per square meter for men and greater than or equal to 88 g per square meter for women [24]. Three consecutive cardiac cycles of all images obtained in the apical axes (four-chamber, two-chamber, and three-chamber views) will be acquired, alongside targeted recordings from the apical four-chamber windows focused specifically on the right ventricle [27]. These recordings will serve to perform advanced deformation analysis of the left ventricular global longitudinal strain, right ventricular free wall strain, and left atrial strain.

To optimize the echocardiographic assessment via speckle tracking, images will be captured at a high temporal resolution of 40–70 frames per second [28]. Subsequently, these digital cardiac cycles will be transferred to a dedicated QLAB workstation (version 10.2, Philips, the Netherlands) for multi-chamber strain analysis. Peak longitudinal regional strain will be measured across the 17 myocardial segments of the left ventricle, and a weighted average will be computed to determine the final left ventricular global longitudinal strain value [25]. Left ventricular global longitudinal strain values higher than minus 16 percent (meaning lower than 16 percent in absolute value) will be classified as abnormal [28]. Right ventricular longitudinal strain will be analyzed utilizing the right ventricle-focused apical four-chamber view, and the average strain value will be obtained from the three anatomical segments of the right ventricular free wall [29]. A free wall right ventricular longitudinal strain value higher than minus 20 percent (lower than 20 percent in absolute value) will be considered abnormal, complying with the 2015 European Association of Cardiovascular Imaging and American Society of Echocardiography chamber quantification guidelines and the recent multinational World Advisory Strain Evaluation study [25,26,30].

Left atrial strain analysis will be executed using the dedicated left atrial automated function imaging software package and will be based on both the left atrium-focused four-chamber and two-chamber views [31]. The total left atrial reservoir strain, which possesses the largest body of clinical evidence supporting its prognostic utility in heart failure, will be reported [32]. The lower normal limit for the left atrial reservoir strain will be set at 16.7 percent [31]. Importantly, these multi-chamber echocardiographic metrics will be utilized to robustly characterize the phenotypic heart failure profiles of the sample and to strictly exclude patients presenting with severe uncorrected valvular diseases or obstructive hypertrophic cardiomyopathy, ensuring absolute hemodynamic safety prior to the exercise protocols.

